#### Qualitative measures

Participants in the intervention group are interviewed individually on all data collections with open-ended questions [42] focused on their experiences of well-being in their present life situation and follow-up questions to gain a greater understanding of their life situation. Participants in the control group are interviewed individually during a shorter interview, focusing on their present life situation. Both groups are interviewed three times.

The interview *prior to the intervention* is related to the participant’s present situation in everyday life, and what causes stress at home and at work, and what contributes to well-being despite living with stress.

The interview *after the intervention* in addition to the same open-ended questions as prior to the intervention, also focuses on the participant’s experiences of the intervention to increase health, well-being and work ability. During this occasion, their photographs from the intervention are used as well and copies of the photographs are also handed over to the data collector as they are data.

The interview *six months after the intervention* focuses on the participant’s present life situation, as well as their perception of photo-supported conversations as intervention. The interview also focused on whether, and if so, how they have been able to use photographs in their everyday life to achieve well-being after the intervention ended.

Each interview is audio recorded and begins with open questions and the participant is encouraged to talk about how they achieve well-being in relation to their everyday life, by describing a certain situation or example. Follow up questions are used as well.

All therapists will, after the final participant, who is receiving their intervention has finished, also be asked to participate in an interview (individual and/or focus group) for investigating their experiences of the intervention, and how to improve the intervention in order to better suit clients with stress-related disorders.

### Sample size

The power calculation for this study was based on the Karolinska Exhaustion Disorder Scale (KEDS) [26]. In a previous study where this instrument was used, the response within each subject group was normally distributed with standard deviation 8.74 [43]. It was thus anticipated that if the true difference in KEDS means (scale on 0–54) between the experimental and control is 7, we will need to study 29 experimental subjects and 29 control subjects to be able to reject the null hypothesis that the population means of the experimental and control groups are equal with probability (power) 0.8. As this study has several timepoints, it is likely that there will be dropouts from the study, and we will thus include a total of 35 experimental subjects and 35 control subjects. The Type I error probability associated with this test of this null hypothesis is 0.05.

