### Analysis

Non-parametric statistics will be used for investigating potential differences between the intervention and control groups in health, and activity-related variables as well as in client satisfaction since the instruments are based on nominal and ordinal scales. Missing data for dropouts will be estimated using the last data obtained before a participant dropped out. The transcribed interviews will be analysed for meanings using thematic [44] and phenomenological [42] analysis. The qualitative data will be analysed for meanings in accordance with the methodological principles of openness, flexibility and a reflective attitude. The analysis is a process defined by a movement between the whole and the parts, with the purpose of identifying a new whole in the phenomenological studies [42] and identifying themes of meanings in the thematic studies [44]. The photographs will be analysed with a semiotic method [45] regarding content and formal aspects, such as shape and color, perspective, spatiality and composition.

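### The stated 29 per arm at power 0.8 does not follow from the test of means that the Sample size section describes: that test needs 26 per arm, and 29 gives power 0.85

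*Protocol article*

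**What the plan says.** The Sample size section of the protocol article bases the calculation on the KEDS, the primary outcome. It reports from a previous study that "the response within each subject group was normally distributed with standard deviation 8.74", supposes that the true difference in means "between the experimental and control is 7" points, and concludes that "we will need to study 29 experimental subjects and 29 control subjects to be able to reject the null hypothesis". The null hypothesis is that "the population means of the experimental and control groups are equal", to be rejected "with probability (power) 0.8". On the error rate it adds: "The Type I error probability associated with this test of this null hypothesis is 0.05". Sidedness is not given. The number is then raised to 35 per arm for dropouts.

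The Analysis section plans non-parametric statistics for the comparisons between groups, "since the instruments are based on nominal and ordinal scales". The Sample size section mentions neither a rank test nor an allowance for one.

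**The concern.** The section gives every input to a standard two-sample calculation except sidedness, and it names the hypothesis. A reader can therefore repeat the calculation, and the answer for the test described is not 29. The gap of 3 per arm by the t-test (4 by the normal approximation) is too large for rounding.

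This paragraph is the article's only justification of the trial's size. Anyone interpreting a null result will return to it to see what the trial was designed to detect, and with what probability. As written, it leaves unclear whether the power, the number, the SD, the difference or the description of the test is at fault. The Analysis section adds to the doubt, because the hypothesis used for planning concerns means and the planned comparison is non-parametric.

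**Working it through.** **Inputs (Sample size section).** SD 8.74; difference 7; alpha 0.05; power 0.80; equal groups. Two-sided testing is assumed because the null is equality; one-sided is tried as well. The standardised difference is d = 7/8.74 = 0.801.

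**Step 1. Attempt to reproduce 29 with the described test of means.**

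- Normal approximation: n per arm = 2(1.960 + 0.842)²/d² = 24.47, so 25.
- t-test by the noncentral t distribution, with 2n − 2 degrees of freedom and noncentrality d√(n/2): n = 25.47, so 26.
- One-sided 0.05, t-test: 19.99, so 20.

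None of these gives 29. A one-sided test widens the gap, so the unstated sidedness cannot explain it.

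**Step 2. What 29 per arm delivers for that test.**

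| n per arm | Noncentrality | Power, two-sided t-test |
|---|---|---|
| 26 | 0.801 × √13 = 2.89 | 0.808 |
| 29 | 0.801 × √14.5 = 3.05 | 0.850 |
| 35 | 0.801 × √17.5 = 3.35 | 0.910 |

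Solving for power 0.85 gives n = 28.99, so 29. For 29 per arm to have power of exactly 0.80, d would have to be 0.749. That means a difference of 0.749 × 8.74 = 6.54 in place of 7, or an SD of 7/0.749 = 9.35 in place of 8.74.

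**Step 3. Whether a rank test explains 29 at power 0.80.** Noether's formula for the Mann-Whitney test with equal groups is N = (z for alpha + z for power)² / [3(p − 0.5)²], where p is the probability that an observation from one group exceeds one from the other. For normal data p = Φ(d/√2) = Φ(0.566) = 0.714, so N = 56.91 in total, or 28.45 per arm: **29**.

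Other common allowances for a rank test, all at power 0.80:

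| Route | n per arm |
|---|---|
| Normal-approximation n × 1.15 | 28.14, so 29 |
| Normal-approximation n / 0.864 (lowest efficiency) | 28.32, so 29 |
| t-test n / 0.955 (efficiency under normality) | 26.67, so 27 |
| t-test n / 0.864 | 29.48, so 30 |

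Several rank-test routes thus reach the stated number from the stated inputs.

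**Step 4. Actual power of a Mann-Whitney test.** Simulation with normal data (20,000 runs per row) gave 0.790 at 26 per arm, 0.799 at 27, 0.815 at 28 and 0.827 at 29. Rounding the scores to whole points within the 0–54 range, with the group means set at 24 and 31 as an assumption, gave 0.831 at 29.

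**The case against.** The strongest defence is that nothing numerical is wrong. The analysis is to be non-parametric, Noether's formula gives exactly 29 per arm at power 0.80, and a journal article need not name its sample-size formula. On that view the SD, the difference, the power and the number are all right. Converting the statement to 26 per arm, or to power 0.85, would then replace a correct figure with a wrong one.

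Much of this stands. A rank-test origin is plausible and cannot be excluded. A reader might infer from the exact match at 28.99 that the calculation was run at power 0.85 and the power misreported; the article does not support that over the rank-test explanation. Leaving out the formula is not itself a fault in an article.

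The defence does not clear the paragraph, because the paragraph does describe its test: it states a null hypothesis of equal population means. If a rank-test formula was used, that description is wrong. If a test of means was used, the power, the number or an input is wrong.

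A reader might also infer that the trial is underpowered, or that planning on means and analysing by ranks costs it power. The figures show neither. On the stated inputs, 29 per arm exceeds 0.80 for both tests.

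**Conclusion.** The point holds as an internal inconsistency. For the test of means described, the requirement at power 0.80 is 26 per arm (52 in total), against the stated "29 experimental subjects and 29 control subjects" (58 in total), which is 12% more (29/26 = 1.12). Equivalently, the power at 29 is 0.85 and not 0.80. The cause is open: misreported power or number, a misreported input, or a rank-test calculation described as a test of means.

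The discrepancy is conservative. At 29 per arm the power is 0.85 for the t-test and about 0.83 for the Mann-Whitney test, so the recruitment target is not threatened. These figures assume two-sided testing, independent observations, normal data with a common SD of 8.74 and a shift of 7 points.

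**What to change.** Retrieve the calculation that was run and restate the paragraph so that hypothesis, test, sidedness, power and number agree with one another and with the non-parametric analysis.

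- If a test of means was used with SD 8.74 and a difference of 7, report 29 per arm as power 0.85, or 26 per arm for power 0.80. Add that a Mann-Whitney test at 29 per arm has power of about 0.83 under normality, so that the figure connects to the planned analysis.
- If a rank-test formula was used, name it, replace the null on means with the one that the rank test addresses, and keep 29 per arm at power 0.80.
- If an input was mistyped, correct it and repeat the calculation.

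The cost is one corrected paragraph. With the stated inputs, the target of 35 per arm does not change.

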### Analysis

Non-parametric statistics will be used for investigating potential differences between the intervention and control groups in health, and activity-related variables as well as in client satisfaction since the instruments are based on nominal and ordinal scales. Missing data for dropouts will be estimated using the last data obtained before a participant dropped out. The transcribed interviews will be analysed for meanings using thematic [44] and phenomenological [42] analysis. The qualitative data will be analysed for meanings in accordance with the methodological principles of openness, flexibility and a reflective attitude. The analysis is a process defined by a movement between the whole and the parts, with the purpose of identifying a new whole in the phenomenological studies [42] and identifying themes of meanings in the thematic studies [44]. The photographs will be analysed with a semiotic method [45] regarding content and formal aspects, such as shape and color, perspective, spatiality and composition.

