### Design and setting of the study

This project is a quasi-experimental pre-test post-test intervention with a control group [19] using quantitative as well as qualitative methods.

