### Context and procedure

The project takes place within the primary healthcare services in two regions in southern Sweden. Five primary care centres recruit participants to the intervention group while five others recruit participants to the control group. Primary care centres who have shown interest in the project have been engaged, and the units themselves chose whether to participate as part of the intervention group or the control group. The primary care centres, however, are comparable in terms of the size of cities where they are situated, socio-economic conditions, and provision of treatment methods. Both groups of participants receive their care as usual in the primary care context.

Potential participants who meet the criteria receive information about the project from a rehabilitation coordinator. When a patient declines to participate, the rehabilitation coordinator informs the project leader about their sex, age, diagnosis, and when possible the reason for declining. This is carried out with the aim of facilitating the exploration of potential differences between those who choose to participate and those who choose not to. When a patient is interested in participating, the rehabilitation coordinator forwards their contact information to the project leader and one of the researchers/project assistants contacts them for a meeting where they receive further information and can ask questions about the study and what participation entails. When agreeing to participate, the patients sign an informed consent and baseline data is collected.

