#### Quantitative measures

Participants in the intervention and in the control group answer the same questions including gender, age, diagnosis, social network, employment, sick leave/not sick leave, work situation and degree of paid work, physical activities, and care consumption. As the project takes place during the pandemic Covid-19, the participants are also asked about whether and how they are affected by the pandemic in their personal lives, as well as in relation to their paid work.

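### Centres chose their own arm, but the named non-parametric comparison gives no stated role to baseline KEDS or the collected covariates, so a difference at entry can be mistaken for, or can mask, an effect

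*Protocol article*

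**What the plan says.** The protocol article, under Design and setting of the study, states: "This project is a quasi-experimental pre-test post-test intervention with a control group". Context and procedure explains how the arms arise: "Five primary care centres recruit participants to the intervention group while five others recruit participants to the control group", and "the units themselves chose whether to participate as part of the intervention group or the control group". A patient's arm is therefore settled by the centre attended. The only assurance of comparability concerns the centres, which are said to be "comparable in terms of the size of cities where they are situated, socio-economic conditions, and provision of treatment methods".

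The Analysis section names one approach for the quantitative comparison: "Non-parametric statistics will be used for investigating potential differences between the intervention and control groups in health, and activity-related variables". The reason given is that the instruments rest on nominal and ordinal scales. The section names no test. It does not say whether follow-up or change scores are compared, and it mentions no baseline term, covariate, matching or centre term.

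The data for adjustment exist. At consent "the patients sign an informed consent and baseline data is collected". Under Quantitative measures the trial records "gender, age, diagnosis, social network, employment, sick leave/not sick leave, work situation and degree of paid work, physical activities, and care consumption", and also asks how the pandemic affects the participant. KEDS and HADS are among the outcome instruments and data collection starts at baseline. The Sample size section treats KEDS, scored 0 to 54, as normally distributed with SD 8.74 and plans for a mean difference of 7.

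**The concern.** Randomisation would make baseline differences a matter of chance. Here a centre's interest, staffing or case mix may have influenced which arm it took, and its patients follow it. Similar city size, socio-economic conditions and treatment provision do not show that patients enter with similar exhaustion, sick leave or prognosis.

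In such a design, adjustment for measured baseline factors is the main analytic protection against confounding by those factors. An ordinary two-group rank test, whether on follow-up or change scores, has no place for covariates. A difference at follow-up then cannot be separated from a difference at entry. The error can go either way: an intervention arm that starts less exhausted can look improved, and one that starts more exhausted can have a real benefit hidden.

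The stated reason for the method does not require this. A proportional-odds model takes covariates and respects ordinality, and the Sample size section already treats the KEDS sum as a quantity with a mean.

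**Working it through.** **Inputs.** From the Sample size section: SD 8.74, target difference 7, alpha 0.05 (two-sided assumed), 29 evaluable and 35 recruited per arm. Assumed, because the document gives neither: the baseline gap b between arms (KEDS points) and the correlation r between baseline and follow-up KEDS. All figures treat patients as independent and ignore centre clustering.

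**The plan's own figure.** n per arm = 2 × (1.96 + 0.8416)² × 8.74² / 7² = 24.5, so 25; the t-test gives 26. The stated 29 corresponds to power of about 0.85 for a t-test. It is conservative and does not bear on this point.

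**Follow-up comparison, arms regressing to a common mean.**
- SE of the difference at 35 per arm: 8.74 × √(2/35) = 2.09.
- Spurious difference with no true effect: r × b. For b = 3 and r = 0.5 this is 1.5 points, and 1.5/7 = 21% of the target.
- Standardised shift: 1.5/2.09 = 0.718. False-positive rate: Φ(−1.96 + 0.718) + Φ(−1.96 − 0.718) = 0.111.
- For b = 4 and r = 0.6: shift 2.4/2.09 = 1.149, false-positive rate 0.210.

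**Simulation over a range of assumptions** (6,000 runs per cell, no true effect, 35 per arm, r = 0.5, common mean). False-positive rates at nominal 5%:

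| Gap b | Mann-Whitney, follow-up | Mann-Whitney, change | Baseline-adjusted regression |
|---|---|---|---|
| 0 | 5.2% | 4.9% | 5.1% |
| 2 | 7.4% | 7.7% | 5.6% |
| 4 | 14.8% | 15.1% | 4.9% |
| 6 | 28.1% | 28.4% | 4.8% |

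Unadjusted change scores are biased by (r − 1) × b, that is −1.5 points for b = 3 and r = 0.5.

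**Masking.** With a true 7-point benefit, 29 per arm and r = 0.5, Mann-Whitney power on follow-up scores is 83% with no gap. It falls to 53% if the intervention arm starts 4 points worse and rises to 96% if it starts 4 points better. The adjusted regression stays at 91–92%.

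**The same case if the gap is stable.** Suppose instead that the two patient populations differ by a constant 3 points that would persist untreated (r = 0.5, 35 per arm).
- Change score: expected difference 3 − 3 = 0, so unbiased.
- Follow-up score: biased by the full 3 points. Shift 3/2.09 = 1.436; false-positive rate Φ(−0.524) + Φ(−3.396) = 0.30.
- Baseline-adjusted regression: biased by (1 − r) × b = 1.5 points. SE about 8.74 × √(1 − 0.25) × √(2/35) = 1.81; shift 1.5/1.81 = 0.829; false-positive rate about 0.13.

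The follow-up-only comparison is therefore biased under both models. The adjusted and change-score analyses are each right under one of them.

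**The case against.** The strongest reply is that a short analysis section in a journal article leaves the test and covariate list to a fuller plan. A reader might infer that the trial has committed itself to an unadjusted test. The article does not say so: it names a class of methods, rank-based analysis of covariance belongs to that class, and the pre-test post-test design makes baseline part of the study. That part stands, and the absence of a covariate list alone would be no finding. What remains is that the article fixes a method class, justifies it by scale type alone, and gives baseline no stated role in a self-selected comparison whose primary inference depends on it.

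A reader might also infer that baseline differences will be reported as an effect. The document does not support that. Whether any gap exists is unknown, the Discussion promises only first insights into a potential effect, and it concedes that other treatments may be hard to control for. It offers no analytic remedy, however.

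The most substantial technical objection is that baseline adjustment is not a cure. It restores 5% error only if both arms regress to a common mean; under a stable gap it is itself biased, and the change score is not. The document cannot settle which holds. This objection stands and shapes the remedy.

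Finally, precision is a secondary argument. Adjustment would raise power at 29 per arm from 0.85 to 0.90–0.96 for r = 0.4 to 0.6, but only with balanced arms and independent patients, and the plan already exceeds its stated 0.8.

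**Conclusion.** The point holds in this form: centres chose their arm, and the only between-group method named gives no stated role to baseline KEDS or the collected prognostic variables. A baseline difference can therefore be mistaken for an intervention effect or can mask one.

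The illustrative size is a 1.5-point bias and a false-positive rate of about 11% at 35 per arm. It rests on an assumed 3-point gap, an assumed correlation of 0.5, independent patients, a follow-up-only comparison, and both arms otherwise regressing to a common mean. With a 2-point gap at the same correlation the rate is about 7%; with 6 points it is about 28%.

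Two stronger conclusions are not supported: that the plan definitely excludes adjustment, and that adjustment would remove the bias. Adjustment addresses measured factors only. Each centre serves one arm, so unmeasured and centre-level differences between the two sets of five remain confounded with the intervention.

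**What to change.** Before the outcome data are analysed, state the following.

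- **Primary analysis:** a regression of follow-up KEDS on arm, adjusted for baseline KEDS and a short fixed list of collected baseline variables, such as age, gender, sick leave, baseline HADS and reported pandemic impact. If ordinality is a concern, use a proportional-odds model with the same terms. Report the adjusted difference (or the odds ratio from the proportional-odds model) with a 95% confidence interval.
- **Sensitivity analyses:** a change-score analysis and the rank test. Say in advance that adjusted and change-score estimates rest on different assumptions in non-equivalent groups, and that disagreement between them will be reported as uncertainty about the effect.
- **Wording:** describe the result as an adjusted association, and name unmeasured and centre-level confounding, with five centres per arm, as remaining.

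This changes the analysis text only and needs no new patients or measurements. The cost is a few degrees of freedom and a more cautious causal statement.

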**Methods/Design:**

This ongoing project has a quasi-experimental design, using quantitative and qualitative methods, and includes patients from primary care centres in two Swedish counties. Seventy patients, 20–67 years, with stress-related illnesses will be recruited. They constitute an intervention group, which receive the intervention together with care as usual, and a control group, which receive care as usual. The intervention, photo-supported conversations about well-being, involves 12 sessions. Care as usual entails medication, occupational therapy, physiotherapy and/or psychotherapy. Data collection is carried out at baseline, and outcomes are assessed directly after the intervention, as well as six months after completion of the intervention. The outcomes are evaluated based on factors related to health, well-being and everyday occupations. Furthermore, data concerning experiences of well-being and perceptions of the intervention will be collected in interviews. The therapists will also be interviewed about their experiences of performing the intervention. Data will be analysed with non-parametric statistics, and qualitative methodology.

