### Data collection

Two researchers ([name], UH), and one project assistant collect the data for the intervention group and three project assistants collect data for the control group. The project assistants are OTs, who are not involved in the intervention. All project assistants have been informed about the project and its aim and the project leader will have continuous contact with them throughout the project to discuss progress and clarify potential issues. The project assistants also meet regularly to discuss together with the researchers and the therapists.

The intervention group meets the data collector prior to the start of the intervention; after the intervention; and 6 months after the performed intervention ended. The control group meets the data collector at the same time points as the intervention group (Fig. 1). In order to protect their confidentiality, all the participants received a code number when recruited, and the list linking names to code numbers is stored separately.

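### Carrying the last score forward for dropouts can bias the KEDS comparison and lets post-intervention scores stand in for six-month results

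*Protocol article*

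**What the plan says.** Under Analysis, the article gives one rule for dropouts: "Missing data for dropouts will be estimated using the last data obtained before a participant dropped out". It states no reason for the rule and no sensitivity analysis. The same section says that "Non-parametric statistics will be used for investigating potential differences between the intervention and control groups", without naming a test.

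Under Data collection, both groups are assessed "prior to the start of the intervention; after the intervention; and 6 months after the performed intervention ended". Under Sample size, the article accepts that "it is likely that there will be dropouts from the study" and raises recruitment from 29 to 35 per group. The planning inputs are that "the true difference in KEDS means (scale on 0–54) between the experimental and control is 7" and that "the response within each subject group was normally distributed with standard deviation 8.74".

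**The concern.** The rule assumes that a patient's KEDS stays fixed from the last visit attended. With three visits this has two consequences:

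- A patient lost before the post-intervention visit keeps the baseline score at both later visits and so counts as unchanged.
- A patient lost between the post-intervention and six-month visits has the post-intervention score used at six months. Persistence is then assumed in exactly the patients in whom it was not observed.

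A fixed course is hard to defend here, because both arms receive care intended to improve symptoms. Equal dropout cannot be taken for granted either. The arms are not randomised, the centres chose their own arm (Context and procedure), and only one arm has 12 added sessions (The intervention). In addition, each carried value enters the test as an observed score, so the uncertainty about it is lost.

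At stake are the primary outcome and the only long-term result. The error can dilute a real effect, create a false one, or overstate how long an effect lasts.

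**Working it through.** **The plan's own figure.** With difference 7, SD 8.74, two-sided alpha 0.05 (sidedness is not stated) and power 0.80, the normal approximation gives n = 2 × (8.74 × (1.960 + 0.842) / 7)² = 24.5, so 25 per group. The t-test needs 26. The stated 29 gives t-test power 0.85, so it errs on the safe side. That gap is a separate matter and does not affect this point. The step from 29 to 35 allows for 6/35 = 17.1% dropout per arm.

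**Assumed inputs (not in the documents).** Usual-care improvement R, early dropout shares p_I (intervention) and p_C (control), and the timing of dropout. E is the true extra benefit of the intervention.

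**Early dropout.** Early dropouts contribute zero change, so the expected LOCF difference is

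(1 − p_I)(R + E) − (1 − p_C)R.

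*No true effect (E = 0).* This reduces to (p_C − p_I)R. With 25% in one arm and 10% in the other, the false difference is 0.15R, to the disadvantage of the arm that loses more:

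| R | False difference | Simulated type I error |
|---|---|---|
| 4 | 0.6 | about 6% |
| 8 | 1.2 | about 8% |

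If p_I = p_C with the same timing, the difference is 0 and the simulated error is 5.0%.

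*True effect 7, unequal dropout.*

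| R | Intervention loses 25%, control 10% | Control loses 25%, intervention 10% |
|---|---|---|
| 8 | 0.75 × 15 − 0.90 × 8 = 4.05 | 0.90 × 15 − 0.75 × 8 = 7.5 |
| 4 | 0.75 × 11 − 0.90 × 4 = 4.65 | 0.90 × 11 − 0.75 × 4 = 6.9 |

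*True effect 7, 6/35 lost early in each arm.* The estimate is 7 × 29/35 = 5.8. The spread also grows, because unchanged patients are mixed with improved ones. At R = 8 the intervention-arm SD becomes √(8.74² + (6/35)(29/35) × 15²) = 10.4, and the control-arm SD becomes √(8.74² + (6/35)(29/35) × 8²) = 9.2. Simulated rank-test power with 35 per arm is about 0.70.

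*Same total, split evenly between the two intervals.* The six-month estimate is 7 × 32/35 = 6.4, with power about 0.80.

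The benchmark is 29 completers per arm with an unbiased difference of 7, which gives t-test power 0.85.

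**Late dropout (an alternative to the early case, not an addition).** Suppose all 6/35 in each arm leave after the post-intervention visit and a 7-point effect has vanished by six months. LOCF then shows 6/35 × 7 = 1.2 points where the truth is 0. The simulated rejection rate is about 8%.

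**Simulation settings.** 35 per arm, normal scores with SD 8.74, within-person correlation 0.6, two-sided Mann-Whitney test at 5%, and dropout unrelated to the patient's own score. For the 5.0% error under equal dropout, the power figures and the late-dropout case, usual care improves by 5 points at post-intervention and 8 at six months.

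**The case against.** The best defence is that the damage is conditional and often modest. With no effect and equal dropout there is none. The false difference scales with R, and many of the scenarios above move the result by about a point. Serious inflation of type I error needs strongly unequal dropout: 30% versus 5% gives about 14%. The study is also non-randomised and claims only first insights. All of this stands, and it limits how firmly the size can be stated. It does not support the rule, whose error depends on a dropout pattern that nobody can know in advance.

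The documents do not support four stronger readings that a reader might draw:

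- **That LOCF contradicts the sample size.** Recruiting 35 to cover losses and also imputing those losses are compatible, since extra patients offset dilution too. The target is a test that succeeds "with probability (power) 0.8", and LOCF with 35 per arm still reaches about that if dropout is split between the intervals.
- **That power falls only to 0.78 when all dropout is early.** That figure uses the shrunken difference of 5.8 but keeps the SD at 8.74. Once the wider spread is counted, power is about 0.70.
- **That the bias favours the intervention.** It can run either way.
- **That patients who stop attending sessions are not followed up.** The article does not say so.

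**Conclusion.** The concern holds in conditional form. The article itself fixes LOCF as the dropout rule and expects dropouts, so this is not a detail left to an unseen analysis plan. The rule biases the KEDS comparison when scores change over time and either dropout differs by arm or a true effect exists. For late dropouts it replaces the six-month result with the post-intervention score.

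On the assumed inputs, a null effect appears as 0.6 to 1.2 points under 25% versus 10% early dropout. A true 7 becomes 5.8 if the planned allowance of 6/35 per arm is all lost early. An effect that has vanished can still show as 1.2 points at six months if the losses are all late. Only the 7, the 8.74 and the 29 and 35 per arm come from the documents. Usual-care improvement, dropout rates by arm, timing and within-person correlation are assumptions, so these figures are illustrations and not forecasts.

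**What to change.** Replace LOCF as the primary rule with a method that is valid under missing at random and uses all observed KEDS scores. The option closest to the present plan is multiple imputation by arm, using earlier KEDS scores and the baseline variables already collected, followed by the planned non-parametric test pooled over imputations. With 35 per arm the imputation model should be kept small. A likelihood-based repeated-measures model is an acceptable alternative.

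Keep LOCF at most as a sensitivity analysis. Add a delta-shift analysis in which the imputed scores of dropouts are worsened or improved by stated amounts, in either arm, because the bias can run either way. Report dropout by arm and by interval.

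The cost is a change of wording and modest programming. No new data are needed. Intervals will be somewhat wider, which reflects the information that is actually missing.
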